### Secondary outcomes

In a similar manner to the primary outcome, the proportion of participants adhering to medication will be assessed at 12 months. Self-reported outcomes will be measured by a trained research assistant during a telephone call at 6 and 12 months. Self-reported medication adherence will be assessed using the Morisky 8-item Medication Adherence Scale [48]. As per the Text4Heart pilot trial [32, 33], adherence to recommended lifestyle behaviors will be measured using a composite health behavior score adapted from the EPIC-Norfolk Prospective Population Study [49]. The following measures will be used to determine participants’ health behavior scores:Smoking status will be measured using three items from a validated smoking history questionnaire [50] including whether participants have ever smoked, have had a puff of tobacco in the last week and when they quit smoking (if appropriate)Physical activity level will be assessed using the Godin Leisure Time Physical Activity Questionnaire (GLTPAQ) [51]. This simple, three-item questionnaire has well-established reliability and validity and has been used in patients undergoing CRAlcohol consumption will be measured using the Alcohol Use Disorders Identification Test alcohol consumption questions (AUDIT-C) [52]—a screening tool designed to assess units of alcohol consumed per week, and identify people who are hazardous drinkers. Index cards referencing standard drink sizes will be used to reduce comprehension errorsFruit and vegetable intake are assessed by two New Zealand-specific questions used in the 2006/2007 New Zealand Health Survey (*n* = 12,488, including adults with CHD) [53]

Participants receive a score on a 4-point scale for each of the four key risk factors, with 1 point each assigned for being a current non-smoker, meeting physical activity guidelines to achieve some health benefits (defined as ≥ 14 units on the GLTPAQ), consuming ≤ 14 standard units of alcohol per week, and consuming at least five servings of fruit and vegetables per typical day.

Using participants’ encrypted National Health Index identification numbers we will be able to obtain clinical data (lipid profiles and blood pressure) from the ANZACS-QI database to maximize collection of these outcomes. Data describing hospital events, clinical information, as well as medication prescribing and dispensing will also be captured. For the purpose of this trial we will access data on lipid profile (total/LDL/HDL cholesterol) and blood pressure, from admission and routine follow-ups. Using ANZACS-QI we will also be able to access information on readmissions and related hospital events.

Intervention delivery costs—including text-message service and per message costs as well as health service staff time for recruitment and program facilitation—will be collected. Any changes in health service utilization observed between intervention and control groups will lead to an estimation of the costs of those changes with the assistance of District Health Board funding information analysts.

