### Intervention and control

All participants will receive usual care, which includes CR support. In addition, those allocated to the Text4Heart II intervention arm will receive a personalized, automated program of CR delivered via text message over 24 weeks. The overall goals of the intervention are to encourage and promote adherence to medication, healthy diet, stress management, regular exercise, reduced alcohol consumption, and smoking cessation (if applicable). Participants will be able choose additional focussed intervention modules at baseline that address risk factors that they identify as most relevant to them, such as physical activity, heart healthy diet, stress management, and smoking cessation.

Participants receive one message per day for the first 12 weeks, a technical support phone call at 12 weeks, and five messages per week for the remaining 12 weeks. Messages will be personalized (including participants’ names) and sent at times to suit participants. The intervention is predominantly unidirectional but participants will be able to reply to text messages and a researcher will answer within 24 h. All participants will be offered brief training at enrollment on how to read, delete, and save text messages. Messages are categorized into four groups (see below). Non-smokers receive one to two general heart health messages, one to two physical activity messages, and one to two dietary messages per week. Smokers receive one general heart health message, one to two physical activity messages, one to two dietary messages, and one to two smoking-cessation support messages per week.

At registration, intervention group participants will select their preferred receipt times for educational (early morning, late morning, early afternoon, late afternoon, or evening) and medication reminder messages to ensure that the timing is appropriate for their needs. Details of the text-message content are provided below.

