### Outcomes

All outcomes are assessed at 6 and 12 months post randomization. The primary outcome is the proportion of participants adhering to medication at 6 months. Medication adherence is defined as SDRs of 80% for statins, antihypertensive, and antiplatelet therapy classes of medication (calculated separately)—consistent with guideline-recommended therapy [47]—where SDR is calculated as the number of days that the supply is obtained divided by the number of days in the observation period. Participants’ community pharmacy dispensing records will be linked using their unique National Health Index number via the National Pharmaceuticals Collection database. This approach has been used successfully in New Zealand to assess statin use [39]. To adjust for days not covered due to death or days spent in hospital these periods are subtracted from the 6-month coverage time. The number of days supplied will be estimated from strength per unit and daily dose variables summed from pharmacy claims during the observation period. To account for any previous supply of the medication (before discharge), medication claims in the 3 months prior to admission are collected. The SDR for each class of medication (statins, antihypertensive, and antiplatelet therapies) will be recorded as secondary outcomes.

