## Discussion

The Text4Heart II trial will determine the effectiveness of a text-message-based intervention in addition to usual care for improving adherence to medication and lifestyle behaviors at both 6 and 12 months. Using the RE-AIM framework this trial will provide much needed data and insight into the potential implementation of Text4Heart II to augment existing cardiac services within two major metropolitan hospitals. The protocol, in accordance with the SPIRIT Statement, includes outcomes from recent systematic reviews of mobile health with the aim of adding quality evidence to the body of academic literature.

This trial addresses many limitations/criticisms of previous mHealth trials [43, 67]; it builds on the Text4Heart pilot trial, is adequately powered, has sufficient duration to elicit behavior change, and the follow-up assessments (6 and 12 months) are long enough to determine the sustained effect of the intervention. We also outline the behavior-change theory used, and intervention content, which will enhance its replicability. Using data linkage (National Pharmaceuticals Collection and ANZACS-QI registries) our Text4Heart II trial will not only provide an objective measurement of medication adherence, but will be one of the first of its kind to provide much needed data on sustained effects on clinical outcomes including hospitalization and mortality. While mHealth is often touted as a low-cost intervention that can be delivered at scale, few studies provide evidence of this. The Text4Heart II trial will also provide much needed data on the cost-effectiveness of this approach, and its potential implementation and scalability as a national service.

In summary, Text4Heart II should produce new knowledge on the effectiveness and cost-effectiveness of an innovative and promising mHealth program to improve self-management of heart disease. It extends previous research by investigating the sustained effects of a text-message intervention, and will offer unique insights into clinical effects. If effective, this approach could substantially reduce deaths and hospital admissions in a group of patients who account for up to one third of all hospital admissions. We will provide much needed insight into the potential of implementing this program at a national level, thereby augmenting existing CVD service delivery.

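### The 12-month dispensing window is not fixed; as most naturally read it includes the 24-week messaging period, so a 12-month difference cannot by itself show a sustained effect

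*Protocol article*

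**What the plan says.** All references are to the Protocol article.

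- **Definition of the ratio (Outcomes).** "SDR is calculated as the number of days that the supply is obtained divided by the number of days in the observation period". The threshold follows: "Medication adherence is defined as SDRs of 80% for statins, antihypertensive, and antiplatelet therapy classes".
- **Length of the primary window (Outcomes).** Days lost to death or hospital stay are removed from the denominator: "these periods are subtracted from the 6-month coverage time". Earlier supply is handled only for medication held before discharge, using claims from the three months before admission.
- **Timing (Outcomes).** "All outcomes are assessed at 6 and 12 months post randomization".
- **The 12-month outcome (Secondary outcomes).** "In a similar manner to the primary outcome, the proportion of participants adhering to medication will be assessed at 12 months". No first day, last day or length is given for this window.
- **Intervention (Intervention and control).** The program is "delivered via text message over 24 weeks".
- **Use made of 12-month follow-up (Abstract and Discussion).** The article says that "the follow-up assessments (6 and 12 months) are long enough to determine the sustained effect of the intervention". Under Evaluating implementation, patient-level Maintenance is evaluated through patient outcomes at 12 months.

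No section describes an adherence window confined to the time after messaging ends.

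**The concern.** A dispensing ratio summarizes an interval, not a time point. A 12-month SDR that starts near discharge or randomization averages the messaging period with the period after it. A participant who collected more medication while receiving messages keeps that credit in the 12-month figure, even if collection then returns to the control level.

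Such a ratio is a sound measure of one-year coverage, but it does not answer whether adherence persists once messages stop. The article gives 12-month follow-up that second meaning without fixing a window that would support it. The trial could therefore report persistence on the strength of supply obtained during the program. It also could not tell an effect that has ended from one that has partly persisted, because both give a 12-month difference smaller than the 6-month one.

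**Working it through.** **1. The plan's own figures.** Inputs from Sample size: 165 per group, two-sided 5%, 80% power, a 15-point difference, control rate 30% (alternatively 60%).

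n per arm = [1.960·√(2p̄(1−p̄)) + 0.842·√(p₁(1−p₁)+p₂(1−p₂))]² / (p₂−p₁)²

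- 30% vs 45%: 163 per arm, 326 in total (stated 330). Power with 165 per arm is 80.6%.
- 60% vs 75%: 152 per arm, 304 in total (stated 304).

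The design figures reproduce, and nothing below changes them.

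**2. Share of a 12-month window spent in messaging.** 24 × 7 = 168 days, and 168/365 = 46%.

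**3. Arithmetic of a cumulative ratio.** With first-period length D₁ and ratio s₁, and second-period length D₂ and ratio s₂:

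SDR(0-12) = (D₁s₁ + D₂s₂)/(D₁ + D₂)

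- Equal halves, s₁ = 1.00: reaching 0.80 overall needs s₂ = 2 × 0.80 − 1.00 = 0.60.
- Split at 24 weeks (168 and 197 days), s₁ = 1.00: s₂ = (0.80 × 365 − 168)/197 = 124/197 = 0.63.
- Equal halves, two people who both have s₂ = 0.65: with s₁ = 0.95 the overall ratio is 0.80 (adherent); with s₁ = 0.80 it is 0.725 (non-adherent). They behaved identically after messaging and are classed differently.

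**4. Size at trial level, by simulation.** The documents give no distribution for the SDR, so these inputs are assumptions: one overall SDR per person (not three classes), two equal half-years, beta-distributed half-year SDRs with precision 3 or 6, and within-person correlation 0.3, 0.6 or 0.9. The months 6-12 distribution is identical in both arms, with adherence at the control rate or 10 points below it. Each arm has 300,000 simulated people. The chance of significance is for 165 per arm at two-sided 5%.

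| Adherent in months 0-6 (control vs text) | Adherent in months 6-12 (both arms) | Cumulative 0-12 month difference (points) | Chance of a significant 12-month result |
|---|---|---|---|
| 30% vs 45% | 30% | 6.9 to 7.9 | 26.7% to 36.5% |
| 30% vs 45% | 20% | 5.7 to 6.3 | 21.5% to 29.3% |
| 60% vs 75% | 60% | 7.6 to 9.4 | 30.1% to 42.4% |
| 60% vs 75% | 50% | 7.5 to 9.4 | 28.3% to 41.0% |

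The simulated months 6-12 difference was within 0.2 points of zero in every setting. The share of the 6-month effect carried forward runs from 5.7/15 = 38% to 9.4/15 = 63%.

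**5. A second model.** Logit-normal coverage (between-person SD 1, half-year noise SD 0.5; control rates 30%, 42.5% and 60%) gives cumulative differences of 7 to 8 points and a 27% to 31% chance of significance, again with no difference in months 7-12.

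**The case against.** **The window is not stated, so a cumulative window cannot be asserted.** This stands. A reader might infer that the article defines the 12-month ratio as counted from randomization, but it does not. Post randomization describes when outcomes are assessed, not where the dispensing window opens. A six-month window ending at month 12 also fits the wording and would fall almost wholly after the program. The cumulative reading is still the more natural one. A 6-month coverage time carried to 12 months suggests a 12-month coverage time. A window opening at month 6 would also need a rule for supply then on hand, and the only such rule concerns supply before discharge.

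**This is detail that a condensed article leaves to the full protocol or SAP.** This stands in part. Those documents are not shown and may settle the window. But the article also says what 12-month follow-up is meant to establish, and on its plainest reading the stated outcome does not establish it.

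**The sustained-effect wording is not tied to the SDR.** This stands. It speaks of follow-up in general, and the Maintenance text speaks of patient outcomes. Self-reported adherence, the health behavior score, lipids and blood pressure at 12 months also bear on persistence. The Hypotheses section claims better adherence at 6 and 12 months, not adherence confined to the time after messaging. The point is therefore limited to claims of persistence that rest on dispensing.

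**The percentages are not false-positive rates.** This stands. A reader might set 22% to 42% against the nominal 5% and infer an inflated type I error. In the scenario used, the cumulative difference is real, so detecting it is a correct rejection; the error would lie in calling it persistence. Nor would a late decline be hidden outright, since the 6-month and 12-month results are both reported and the fall from 15 points would be visible. The scenario is also an extreme one: the full design effect, then none.

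**A second-half window with carry-in lets messaging-period supply back in.** This is correct as far as it goes, and the fix therefore includes an analysis without carry-in.

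**Conclusion.** The point holds in a limited form. The observation window for 12-month dispensed adherence is not fixed. On the most natural reading it contains the messaging period, and a difference on that measure could not by itself support a sustained effect or patient-level Maintenance.

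That a cumulative ratio carries first-half supply forward is plain arithmetic. The trial-level size, about 6 to 9.5 points from a 15-point effect that ends at 6 months, rests on the assumed SDR spread, the within-person correlation and the complete absence of a later effect. Two different models agree on the order of magnitude. If the full protocol or SAP already uses months 6 to 12, the problem disappears and one clarifying sentence is enough. The matter concerns one secondary outcome and how it is interpreted.

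**What to change.** 1. State the first and last day of the 12-month observation window.
2. Base any dispensing claim about a sustained effect or Maintenance on the proportion with SDR of at least 80% over the post-intervention period, about day 183 to day 365. Adjust the denominator for death and hospital days as in the primary outcome.
3. State a rule for supply on hand at day 183, and add a sensitivity analysis without that carry-in. Carrying stock in credits some messaging-period supply to the later window; leaving it out can make a well-stocked participant look uncovered. Reporting both shows how much the result depends on the choice.
4. Report the cumulative 0-12 month SDR alongside, labelled as one-year coverage.

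The cost is one extra derived window on data already linked, plus a few lines of text. The downside is that the post-intervention difference will usually be smaller than the cumulative one.

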### Adverse events

All participants will continue with their usual care for ACS. No individual clinical advice is given through the pre-programmed text messages. We will be evaluating hospitalizations or health service utilization as part of the outcomes specified above.

#### Cost-effectiveness analysis

This analysis will adopt a health system perspective. We will use the EQ-5D—a generic and validated measure of quality of life for which reliable New Zealand population preference values are available—to obtain a single preference index for calculation of Quality-adjusted life-years (QALYs) to assess cost per QALY, for comparison with other programs. The incremental cost of making one extra participant adherent to CR using the intervention compared to usual care will be calculated. Ninety-five percent confidence intervals for incremental cost-effectiveness ratios, 95% confidence ellipses on the incremental cost-effectiveness plane, and cost-effectiveness acceptability curves will be calculated to compare the intervention with usual care. Markov modeling will combine these data with other information from a systematic review of cost-effectiveness studies of CR to identify the long-term cost-effectiveness of the intervention.

### Data management

Data will be entered into an electronic collection system provided by Enigma Solutions which will be linked to the ANZACS-QI register. Range checks will be implemented and 10% of data will be checked for consistency against source data.

### Evaluating implementation

We propose using the RE-AIM model proposed by Glasgow and colleagues [34, 54] to determine uptake and sustainability of the intervention. The RE-AIM framework—which emphasizes collecting information about the Reach, Effectiveness, Adoption, Implementation, and Maintenance of an intervention—is an evaluative framework for guiding the evaluation and reporting of health intervention effectiveness [55]. Further, RE-AIM provides a framework for determining which programs work under real-world conditions and which programs should be sustained. The RE-AIM framework is an ideal tool to use as the basis for planning and evaluating the success of mobile phone self-management interventions [56, 57]. It also aligns with systems-based approaches and allows for assessment of vertical (e.g., adoption decisions within a given organization) and horizontal (e.g., adoption across different sectors) components [58]. The RE-AIM framework includes both individual- and setting/staff-level variables. Two dimensions operate at the individual level (reach and effectiveness).

A mixed-methods approach [59] will be used to assess the key components of RE-AIM. Qualitative and quantitative data will be combined to thoroughly understand the extent to which the self-management intervention could be successfully implemented within the New Zealand health context [60]. To achieve this, data will be collected on each RE-AIM dimension as proposed by Kessler et al. [61] and Glasgow [60]. Some of these data will be collected as part of the trial (e.g., data to inform reach, effectiveness and costs/resources). Additional data will be collected specifically for the RE-AIM analysis (detailed below).

To determine intervention reach, we will assess the number of people who participate as a proportion of those who are eligible, compare the characteristics of those who do and do not participate, and provide detailed information of reach and recruitment issues [62, 63]. To achieve this, all potential participants approached about the study will be screened and basic information collected. Those who decline participation will have their information permanently de-identified. Screening information will be used to determine the representativeness of those who agree to participate compared to those who decline. Qualitative data will be gathered from those who decline about their reasons for choosing to not participate. For those who agree, a brief semi-structured interview will be conducted to determine their perspectives of the proposed intervention, their current self-management behaviors, and any concerns they might have that would have impacted on their involvement or adoption.

In addition to the primary outcome, biological-, psychosocial-, demographic-, and program-specific parameters will be assessed as potential moderators of intervention effectiveness.

RE-AIM dimensions Adoption, Implementation, and Maintenance will be assessed from both provider and organizational perspectives [54]. Key informant interviews will be conducted with stakeholders (medical practitioners and allied health staff) to obtain qualitative data from providers across these three RE-AIM dimensions, to determine factors that may enhance organizational adoption and maintenance, and potential adaptations to heighten the likelihood of consistent delivery across providers and locations. Quantitative assessment of implementation will be determined by measuring text-message responses where appropriate. Maintenance at the organizational level will be determined by conducting key informant interviews with stakeholders (e.g., chief executive officers) as well as government and non-government agencies (Ministry of Health, Heart Foundation) examining potential sustainability options for each organization [64]. To evaluate Maintenance at the patient level, patient outcomes will be measured at 12 months via ANZACS-QI. Long-term attrition (%) and differential rates by patient characteristics or treatment condition will be examined. At the organizational level, we will collect data on whether the interventions were sustained at more than 6 months post study funding, or which elements were retained after the program was funded.

Qualitative data collection and analysis will be conducted by a trained and experienced researcher. Interviews will be digitally recorded and transcribed. Data will be entered using NVivo software to enable qualitative analysis. An inductive analysis approach will be used to identify the key themes to emerge from the data. These data will be collated according to each domain of the RE-AIM framework. These data sources will be combined and—together with the advisory group—investigators will make recommendations to determine the extent to which the self-management intervention achieved the desired RE-AIM outcomes. This approach has been successfully used with other behavior-change interventions and will also be valuable for informing optimal scenarios for funding and implementing this self-management program [54, 65, 66].

